### Planned analysis

Descriptive summaries of socio-demographic and clinical data will be provided for all subjects at different time points. These include means and standard deviations, or proportions. The clinical ratings will be summarized in terms of the total score, and the proportion of patients improving from baseline. An “intention to treat” approach will be employed. Baseline qualitative variables will be compared between the intervention and control group by chi2 test. The quantitative variables will be compared using *t*-test and Mann–Whitney *U* test. The quantitative primary and secondary outcomes measures will be compared using general linear model (GLM) repeated measure analysis. Length of stay will be assessed in each period of follow-up; we analyze it both as the cumulative hospital stay (using *t* test) and as the stay in each follow-up period. The second analysis will be performed by repeated measures analysis of variance analysis.

We calculate all direct medical and non-medical costs of care from a societal point of view. To do that, total costs of care (not just out-of-pocket payments) were considered. Medical costs included costs of hospitalization, outpatient and community visits, family psychoeducation, social skills training, medicine, and complementary-alternative therapies in both groups and also all payments for providing specific healthcare of the interventions. Non-medical costs included costs of transportation of patients, caregivers and healthcare teams (in the intervention group). We divide incremental direct costs (Costs in the intervention group minus control group) by incremental effects (based on primary and secondary outcomes) to calculate incremental cost-effectiveness ratio (ICER). Statistical package for social sciences (SPSS version 18.0) will be used for data analysis.

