### Data collection/Management process

The primary outcome measures were the length of hospital stay and any psychiatric rehospitalization during the 12 months post discharge. The secondary outcome measures included: 1) symptom severity, 2) clinical global impression of the illness, 3) global functioning, 4) quality of life, and 5) patients’ satisfaction with service. We also performed a direct cost-effectiveness analysis.

Data were collected from the intervention and control groups at time of index admission, discharge and at each follow-up point. Follow-up ratings in Iran and Nour hospitals were scheduled 3, 6, and 12 months and in another one (in Roozbeh hospital) at 4, 8 and 12 months following discharge and were performed in the outpatients department or at home by an experienced and trained clinician.

We used the following tools in baseline assessment, when the patients were discharging from the hospital, and the follow-up ratings: the Positive and Negative Symptoms Scale (PANSS) for psychotic symptoms
[57], the Young Mania Rating Scale (YMRS) for manic symptoms
[58], the Hamilton Depression Rating Scale (HDRS) for depressive symptoms
[59], the Clinical Global Impression (CGI) for illness severity
[60], the Global Assessment of Functioning (GAF) for global functioning
[61], the Farsi translation World Health Organization Quality of Life (WHOQOL-BREF) for quality of life
[62] and Client Satisfaction Questionnaire (CSQ-8) for the assessment of patients' satisfaction with the services
[63].

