### Sample size calculation

Sample size calculation was based on the length of hospital stay as the primary outcome measure. The following formula was used for the calculation:

$$n=2{\left[z_{\left(1-\alpha /2\right)}+z_{\left(1-\beta \right)}\right]}^{2}\times \left(SD^{2}\right)/d^{2}$$

where d = (delta [difference]). Here delta equals to our estimate of the difference between length of hospital stay in experimental and control groups. In a study on the efficacy of home care service
[64], it was shown that the mean hospitalization days in the home care group was about a third of that in the treatment as usual group (14.5 vs. 41.7 days). Also in an unpublished study ([name], Personal Communication), we found that mean hospital stay of patients with severe mental disorders equals to 45 days with the SD of 18 days. For the present study we aimed for a more conservative and still important difference. We hypothesized that the home care program leads to at least 10 days reduction in hospital stay (×1- × 2 = 10, SD = 18, Cohen's d = 0.6). Sample size was estimated 45 per group; assuming about 30% losses to follow-up, sample size was calculated 60 per group (in total: 120). In one of the centers (Roozbeh hospital) the sample size was 80 per group (in total: 160), because the caseload was higher that allowed recruiting more patients in the same period.

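### The secondary rating scales are compared by repeated-measures GLM with no treatment contrast named and no adjustment for the discharge score

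*Protocol article*

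**What the plan says.** Under Planned analysis, one sentence gives the inferential method for the quantitative scales: "The quantitative primary and secondary outcomes measures will be compared using general linear model (GLM) repeated measure analysis". It lists neither the levels of the time factor nor the effect that decides.

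Under Data collection/Management process, the scales are secondary ("The secondary outcome measures included: 1) symptom severity, 2) clinical global impression of the illness, 3) global functioning"). They are rated before the intervention starts and again afterwards: "We used the following tools in baseline assessment, when the patients were discharging from the hospital, and the follow-up ratings". There are three follow-up ratings, "scheduled 3, 6, and 12 months and in another one (in Roozbeh hospital) at 4, 8 and 12 months following discharge".

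For these scales the baseline rating has a stated use only in a descriptive summary: "The clinical ratings will be summarized in terms of the total score, and the proportion of patients improving from baseline". No covariate role is given.

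Length of stay is treated separately: "Length of stay will be assessed in each period of follow-up; we analyze it both as the cumulative hospital stay", and also period by period. Planned analysis further divides incremental costs by incremental effects on primary and secondary outcomes to obtain ICERs.

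**The concern.** A repeated-measures GLM with two groups prints a between-group effect and a group-by-time interaction. They answer different questions, and the article does not say which is the comparison of aftercare with TAU.

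If the discharge rating is a time level, neither line fits the question well. The group effect averages in a time point at which randomisation makes the expected difference zero. The interaction tests for any difference in profile and gives no signed estimate. If the discharge rating is left out, the group effect is undiluted, but the information in the discharge score is wasted.

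The conclusion on a scale could then depend on which line is read, and real gains in functioning or quality of life could be missed. The ICERs on secondary outcomes need one signed difference per scale, and the interaction supplies none.

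**Working it through.** **The plan's own figure.** The only sample size is for length of stay: a programme that "leads to at least 10 days reduction in hospital stay", with "SD = 18, Cohen's d = 0.6". With two-sided 5% and 80% power (both assumed), n = 2(1.96 + 0.84)²/0.6² = 43.6, so 44, or 45 with the t distribution. The stated 45 is reproduced from the rounded 0.6; the unrounded 10/18 gives 51. This figure does not concern the rating scales, for which no effect size, correlation or power is stated.

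**Assumptions.** Complete data, equal variances (SD 1), exchangeable correlation ρ of 0.3, 0.5 or 0.7, no difference at discharge, two-sided 5%. The effect is set so that the follow-up mean, adjusted for the discharge score, has 80% power (standardised difference 2.80). The group size then cancels: exact results for 45, 60 and 160 per group agree to within about 1 point.

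**Variances.**
- Follow-up mean adjusted for discharge: v = (1 + 2ρ)/3 − ρ²
- Follow-up mean unadjusted: (1 + 2ρ)/3
- Mean over four levels: (1 + 3ρ)/4

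**Group effect, discharge as a level.** A constant difference d is estimated as (0 + d + d + d)/4 = 0.75d. At ρ = 0.5, v = 0.667 − 0.25 = 0.417 and the four-level variance is 0.625. The standardised difference is 2.80 × 0.75 × √(0.417/0.625) = 1.71, and power is Φ(1.71 − 1.96) = 40%.

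**Group effect, three follow-ups only.** At ρ = 0.5: 2.80 × √(0.417/0.667) = 2.21, power 60%. Here the loss comes only from not adjusting for baseline. The interaction among the three follow-ups carries no signal at all for a constant difference.

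**Interaction, discharge as a level (3 df).** Noncentrality λ = 7.85 × k × v/(1 − ρ). Here k is the sum of squares of the effect profile about its own mean, divided by the squared follow-up mean effect.
- Constant, profile (0, 1, 1, 1): k = 0.75
- Even growth, profile (0, 1/3, 2/3, 1), as in linear growth over 4, 8 and 12 months: k = 0.556/0.444 = 1.25

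At ρ = 0.5, v/(1 − ρ) = 0.833, so λ = 4.9 (44%) for the constant effect and 8.2 (67%) for even growth.

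| ρ | Group, 4 levels | Group, 3 follow-ups | Interaction, constant | Interaction, even growth | Adjusted follow-up mean |
|---|---|---|---|---|---|
| 0.3 | 53% | 72% | 34% | 54% | 80% |
| 0.5 | 40% | 60% | 44% | 67% | 80% |
| 0.7 | 26% | 41% | 53% | 77% | 80% |

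The group columns are the same for both shapes, because the four-level mean is always 3/4 of the follow-up mean.

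**Two checks on the range.**
- With a larger effect the loss shrinks. At 0.6 SD, constant, ρ = 0.5 and 45 per group, power is 76% (group), 84% (interaction) and 99% (adjusted mean).
- Linear growth over 3, 6 and 12 months, profile (0, 1/4, 1/2, 1), gives k = 0.547/0.340 = 1.61 and λ = 8.0, 10.5 and 13.0. Interaction power is then 66%, 79% and 87%, so at ρ = 0.7 it passes the adjusted mean. It does not pass the adjusted month-12 difference. The standardised value of that difference is 2.80√v/(0.583√(1 − ρ²)) = 3.35, 3.58 and 3.74, which gives 92%, 95% and 96%.

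**Disagreement and false positives.** In 4,000 simulated trials per setting (45 per group, discharge as a level, constant effect), exactly one of the two tests was significant in 49-52%. With no effect, at least one was significant in 9-10%. Two independent tests would give 1 − 0.95² = 9.75%.

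**ICER.** With discharge as a level, the effect in the denominator is 0.75 of a constant follow-up effect, so the ratio is inflated by 1/0.75 = 1.33.

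**The case against.** The strongest reply is that the article never says that discharge is a time level. It says when the scales are collected, not how the discharge score enters the model. That is correct: a reader might infer inclusion from the two sections together, but the dilution to 3/4 is conditional on it. The unnamed contrast and the missing adjustment do not depend on it.

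A reader might also conclude that each test loses about half the available power. That holds only near correlation 0.5 with a constant effect and a benchmark near 80%. Elsewhere the interaction may lose little, and against the follow-up mean it may lose nothing.

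A reader might further infer a doubled false-positive rate. The 9-10% needs a rule of claiming success on either test, and the plan states no such rule.

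It can also be said that naming a contrast for each secondary scale is detail that an article leaves to the analysis plan. That has weight and limits the grade. But the article does state the method, as the sole inferential comparison of these scales, and a better one is available on the same data. The planned means and SDs at each time point would show size and direction, but only descriptively.

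Finally, the primary outcome is not affected by dilution. The quoted sentence covers it, but stay after discharge has no pre-intervention level, and the cumulative stay has its own t test.

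**Conclusion.** The point holds in a limited form. The stated GLM leaves the treatment comparison for the secondary scales undefined and makes no use of the discharge score for adjustment. If discharge is a level, the group effect has 26-53% power and the interaction 34-77%, where the baseline-adjusted follow-up mean has 80%. If it is not, the group effect has about 60% at correlation 0.5 with a constant effect.

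These figures rest on assumed correlations and effect shapes, complete data and an effect that puts the benchmark at 80%; none of these is in the article. The upper end for the interaction applies to even growth and rises if growth is concentrated late. What does not depend on those assumptions is that the two tests can disagree and that the interaction gives no signed effect for an ICER. The matter concerns secondary outcomes and their ICERs. It is a worthwhile improvement and no threat to the primary result.

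**What to change.** In Planned analysis, state that each rating scale is analysed with the post-discharge ratings only as the repeated outcome and the discharge score as covariate. Name one aftercare-minus-TAU contrast per scale, either month 12 or the average over follow-up, with its 95% CI. Use the same contrast in the ICER for that scale, and report the group-by-time interaction as descriptive.

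The choice of contrast should follow the expected course. The follow-up average suits a steady benefit: where it has 80% power, the adjusted month-12 difference has only 50-59% over the same correlations. Month 12 suits a benefit that builds up.

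The cost is one sentence. The data are already collected and the software stays the same. The small downside is that the overall profile test is no longer inferential.

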### Ethical considerations

Before the conduct of the study, patients and their family members were thoroughly informed regarding the services that were provided for them. Then, written informed consent was obtained from the patients and their guardians. The obtained data were strictly confidential. It was well explained to patients that they have the right to quit participating in the study any time they want and if so, they can continue receiving routine conventional therapy offered by the hospital (out-patient or in-patient). In addition, patients were hospitalized whenever it was necessary. If treatment modalities like electroconvulsive therapy were necessary, patient underwent the required treatment. No cost was imposed on patients and all the expenses like the cost of the home visit (but not the cost of medications or hospitalization) were provided from the study budget. No patient group was disadvantaged as clinical care in these patients varies.

Questionnaires were filled out anonymously and were specified only by a code. Using that code, data were entered the database software. Patients’ medical records were maintained in a locked up cabinet in a room in the mental health clinic.

Moreover, in each center there was an external supervisor assigned from Vice Chancellor of Research who oversaw the whole procedure of research and he received progress reports of the project in each center and if necessary he had to make decisions with regard to undesired events.

The study was approved at Tehran University of Medical Sciences Ethics Committee ref: 130-6-2441, and is fully compliant with the Helsinki declaration 2008. The trial is registered with Iranian Registry for Clinical Trials and the allocated unique ID number is IRCT201009052557N2.

## Discussion

This paper presents a protocol for an RCT of aftercare services delivered to patients with severe mental illnesses by community mental health teams within patients' home or at the outpatient clinic. Also, the trial tries to understand patients’ satisfaction of receiving this form of intervention. Determining the clinical effectiveness and cost analysis of the intervention will help policy makers at the Ministry of Health as well as clinicians and other care-providers to improve their program planning.

## Abbreviations

SMI: Severe mental illness; ACT: Assertive community treatment; CMHT: Community mental health team; PANSS: Positive and negative symptoms scale; YMRS: Young mania rating scale; HDRS: Hamilton depression rating scale; CGI: Clinical global impression; GAF: Global assessment of functioning; WHOQOL-BREF: World health organization quality of life; CSQ-8: Client satisfaction questionnaire; GLM: General linear model; RCT: Randomized clinical trial.
